##### Statistical analyses

We will follow the CONSORT guidelines for randomized controlled trials [49]. The statistical analysis of the data will be conducted by a statistician blinded to the treatment group. The primary outcomes will be the total HADS score and secondary analysis will be conducted using the Anxiety and Depression subscales. Intention to treat will be used for our primary analysis, where subjects will be analysed in the groups they were randomized regardless of compliance of having dropped out. The mixed effect model, where subjects are the random effects, time (baseline, 12 weeks and 36 weeks) and group (CaCBT and Standard CBT) as well as the interaction between time and group will be entered as fixed factors, with gender and baseline HADS as covariates. The significance of the interaction between group and time tests for difference in HADS score at 3 or 6 months and will be used to declare the intervention effective. Since recruitment will be conducted in 3 sites, these sites will also enter the model as random effects. We will also control for therapists variation by coding them as a variable in the dataset, then adding them to the model as a random effect. Mixed effect models estimated through maximum likelihood are able to account for dropouts under the assumption they are missing at random (MAR) [50, 51]. Comparison between dropouts and completers will be conducted at baseline to look at evidences of differences between them, and if significant differences are found, they will be accounted for by adding the variable as a control in the model. A significance level of 0.05 will be used to declare the CaCBT performs better than standard CBT. A diagnostic analysis will be conducted using Cook’s distance to detect possible influential data points, and if any is found, results without these subjects will be also presented if they lead to meaningfully different conclusions. Residuals will be checked for heterogeneity of variance that, if found, will be addressed by the use of robust “sandwich” type standard errors. We may also conduct a sensitivity analysis using completers only with ANCOVA and inverse propensity weighting, where weights are the estimate probability of dropping out estimated by a logistic regression model having baseline characteristics as predictors of the subjects. Such ANCOVA has the HADS score at the end of the trial as the outcome and HADS at baseline as the covariate, while also controlling for gender and sites. This approach is suggested in [52]. Finally, a similar ANCOVA without weights will be conducted using last observation carried forward (LOCF) and all subjects. If more than 10% of the subjects are found to be non-compliant, a per-protocol analysis will also be conducted where non-compliant subjects are removed. All these extra analyses will provide information on the robustness of the primary analysis through the mixed effect model.

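### The primary mixed model allows one common within-patient correlation over baseline, 12 and 36 weeks; if correlations decay, the 36-week interval is too narrow and the missing-at-random assurance is overstated, though the deciding joint test is little affected

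*Protocol article*

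**What the plan says.** The Statistical analyses section (Phase 2) describes "The mixed effect model, where subjects are the random effects, time (baseline, 12 weeks and 36 weeks", with group and the group-by-time interaction as further fixed terms and gender and baseline HADS as covariates. Of sites it says that "these sites will also enter the model as random effects", and it handles therapists by "adding them to the model as a random effect". Both act between patients. No random slope and no residual covariance structure is named.

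The test on which success is decided is the joint interaction: "The significance of the interaction between group and time tests for difference in HADS score at 3 or 6 months and will be used to" (the sentence ends with the verdict of effectiveness). The level is fixed by "A significance level of 0.05 will be used to declare the CaCBT performs better than standard CBT".

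Two further statements bear on the covariance. On missing data: "Mixed effect models estimated through maximum likelihood are able to account for dropouts under the assumption they are missing at random (MAR"). On model checking: "Residuals will be checked for heterogeneity of variance that, if found, will be addressed by the use of robust “sandwich” type standard errors".

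**The concern.** A random subject effect with independent residuals makes all pairs of visits equally correlated. The visits are unevenly spaced (0, 12 and 36 weeks) and the first precedes therapy. It is plausible that the two post-therapy scores correlate more closely with each other than baseline does with week 36. The model then replaces the individual correlations by their average.

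Two things are at stake. The first is the 36-week contrast and its interval, which will carry the interpretation because the interaction is said to detect a difference at either visit. The second is the dropout assurance. Likelihood fills in missing 36-week scores from the assumed correlations, so its protection under missing at random depends on the covariance being right. The article allows for up to 30% attrition, and both its Background and its Discussion expect the adapted therapy to lose fewer patients. Dropout that differs by arm is therefore the plan's own expectation.

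**Working it through.** **The plan's own figure.** For d = 0.68, two-sided 5% and 90% power: 2 × (1.960 + 1.282)² / 0.68² = 45.4, so 46 per group. The noncentral t gives 47, and power at 48 is 0.909. The stated 48 per group is reproduced. Then 96 / 0.7 = 137.1, or 138 with equal arms, close to the planned 140. None of this involves a correlation between visits.

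**Inputs.** From the article: visits at 0, 12 and 36 weeks, 70 per arm, SD 3.5, level 0.05 (taken as two-sided). The SD is given for the depression subscale, while the model's outcome is total HADS. Ratios and error levels below do not depend on the SD; results in points do. All correlations are assumptions.

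**36-week standard error, complete data, equal SDs.** Write ρ̄ for the mean of the three correlations.
- The random-intercept model takes the variance of a change score as 2·SD²·(1 − ρ̄). The true value for 36 weeks minus baseline is 2·SD²·(1 − ρ(0,36)).
- Ratio of model to true standard error = √[(1 − ρ̄) / (1 − ρ(0,36))].
- Level of the contrast = 2·[1 − Φ(1.96 × ratio)].

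| ρ(0,12) / ρ(0,36) / ρ(12,36) | Ratio | Level at 36 weeks |
|---|---|---|
| 0.50 / 0.40 / 0.60 | √(0.50/0.60) = 0.91 | 7.4% |
| 0.40 / 0.30 / 0.65 | √(0.55/0.70) = 0.89 | 8.2% |
| 0.50 / 0.35 / 0.65 | √(0.50/0.65) = 0.88 | 8.6% |
| 0.60 / 0.36 / 0.60 | √(0.48/0.64) = 0.87 | 9.0% |
| 0.50 / 0.50 / 0.50 | 1.00 | 5.0% |
| 0.40 / 0.50 / 0.50 | √(0.533/0.50) = 1.03 | 4.3% |
| 0.40 / 0.60 / 0.40 | √(0.533/0.40) = 1.15 | 2.4% |

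The standard error is too small exactly when ρ(0,36) lies below the average of the other two correlations.

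In points, for the third row: √(4 × 12.25 × 0.50 / 70) = 0.59 against √(4 × 12.25 × 0.65 / 70) = 0.67. Simulation at 70 per arm gave 0.586 against 0.67 to 0.69, and a level of 8.7 to 8.8%.

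**Joint interaction test.** Its null distribution is a weighted sum of two chi-squares whose weights add to 2, because the model gets the average variance of the contrasts right. For the third row the weights are about 0.65 and 1.35. The large-sample level is 5.2 to 5.6% over the first four rows, and 5.0 to 5.9% over all correlation and SD patterns tried.

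**Missing 36-week scores.** A common correlation of 0.50 predicts week 36 with weights ρ̄/(1 + ρ̄) = 0.33 on baseline and 0.33 on week 12. Under 0.50 / 0.35 / 0.65 the correct weights are:
- baseline: (0.35 − 0.50 × 0.65) / (1 − 0.25) = 0.03
- week 12: (0.65 − 0.50 × 0.35) / (1 − 0.25) = 0.63

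The simulations had no true effect and no baseline covariate, and dropout at week 36 depended on the 12-week score.
- About 40% against 16% dropout: bias 0.13 to 0.14 points with the random intercept, 0.03 or less with an unstructured covariance. A separate check gave about 0.17.
- About 32% in each arm with opposite dependence on the score (a stress case): bias 0.30 to 0.42 points, and 8.6 to 10.4% joint rejection even with subject-clustered sandwich errors.
- Truly equal correlations: bias near zero.

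**Sandwich errors.** Clustered by subject, they brought the 36-week standard error to 0.98 to 1.01 of the truth and its level to 4.9 to 5.9% (no baseline covariate, same dropout mechanism in both arms). The clause's trigger is unequal variance, and none of the table's patterns has that.

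**The case against.** **The article does not fix the residual covariance.** A structured residual can sit beside a subject effect, and an article may leave that to the full plan. This stands as a limit: if the full plan specifies such a structure, the point falls away. But the article lists its random effects one by one and claims dropout protection for the result, so it states a model rather than staying silent.

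**The direction is not known.** This also stands. With equal SDs, a standard error that is too large needs baseline to correlate more with week 36 than the other two pairs do on average, which is the reverse of ordinary decay. With baseline SD 2.5, follow-up SD 3.5 and all correlations 0.5, the ratio is 1.04. With those SDs and 0.40 / 0.30 / 0.65 it is still 0.92 (level 7.3%).

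**A reader might infer that the trial's 0.05 level is breached.** The documents do not support that. Success rests on the joint interaction, which barely moves with complete data. Simulations with missing-at-random dropout and baseline HADS as covariate do give joint levels of 7.6 to 8.0%, but about 7 to 8% also appears when the correlations are truly equal. That excess comes mostly from baseline being both an outcome level and a covariate, not from the correlation pattern.

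**Safeguards exist.** Subject-clustered sandwich errors would repair the 36-week standard error, and the planned ANCOVAs do not use this covariance. But the sandwich clause is conditional on unequal variances, its clustering is not spelled out, and it does not remove bias. The ANCOVAs are supporting analyses, one of them optional.

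**Conclusion.** The point holds in conditional form. As written, the primary model imposes one variance and one correlation on three unevenly spaced visits. Under ordinary decay (assumed), the model-based 36-week standard error is about 9 to 13% too small and a 36-week contrast runs at about 7 to 9%. With complete data the deciding joint test stays at about 5 to 6%.

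Under missing-at-random dropout that differs between arms, the 36-week effect is biased by about 0.1 to 0.2 points at SD 3.5. That is 4 to 8% of the 2.4-point target (0.1/2.4 and 0.2/2.4), and more in the stress case. The statement that maximum likelihood accounts for such dropout is therefore true only if the covariance is adequate. This is worth correcting before analysis but does not by itself undermine the decision rule.

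**What to change.** Replace the random subject intercept by an unstructured within-patient covariance, fitted by REML with Kenward-Roger degrees of freedom. Keep gender, site and therapist, and use baseline HADS only once, in one of two ways:

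- as an outcome level, with a 3×3 covariance over 0, 12 and 36 weeks and no baseline covariate, keeping the joint group-by-time test; or
- as a covariate (preferably with its own slope at each visit), with 12 and 36 weeks as outcomes, a 2×2 covariance and a joint test of the group effects at both visits. The interaction alone would then only compare the two effects with each other.

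Using baseline once is necessary. With baseline on both sides, a slope of 1 makes every baseline residual zero, so a free baseline variance collapses and the likelihood has no maximum.

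Name a simpler structure with subject-clustered sandwich errors as the fallback for non-convergence. State that the missing-at-random claim rests on this covariance.

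The cost is a few sentences of analysis wording and six covariance parameters (3×3) or three (2×2) in place of two, well within what 140 patients support. If correlations decay, the 36-week interval will be slightly wider. Sample size and data collection do not change.

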##### Sample size calculation

The sample size was calculated using a comparison between group change in the HADS Depression subscale scores. With a 5% significance level and 90% power, we determined that 48 subjects per group will be required for the trial, in order to detect a standardized effect size Cohen’s *d* = 0.68, which is equivalent to a difference in HADS score at the end of the trial of around 2.4 points, assuming a standard deviation of 3.5 found in previous studies from our lab that used the same outcome. To account for up to 30% attrition, we plan to recruit a total of 140 participants into the study.

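### The primary mixed model uses baseline HADS both as a response and as a covariate, so the deciding test gains nothing from the adjustment and is unreliable under the 30% dropout that the plan allows for

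*Protocol article*

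**What the plan says.** All of this is in the Statistical analyses section of the protocol article unless another section is named.

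- **Response and fixed factors.** The model has "time (baseline, 12 weeks and 36 weeks) and group (CaCBT and Standard CBT) as well as the interaction between time and group". Baseline is therefore one of three response times.
- **Covariates.** These terms "will be entered as fixed factors, with gender and baseline HADS as covariates". No baseline-by-time term is mentioned.
- **Random terms.** "The mixed effect model, where subjects are the random effects"; site and therapist are further random effects.
- **Decision rule.** "The significance of the interaction between group and time tests for difference in HADS score at 3 or 6 months", and this interaction decides whether the intervention is called effective. With three time levels and two groups it has 2 degrees of freedom.
- **Dropout.** "Mixed effect models estimated through maximum likelihood are able to account for dropouts under the assumption they are missing at random (MAR". If dropouts and completers differ at baseline, "if significant differences are found, they will be accounted for by adding the variable as a control in the model".
- **Safeguards.** Robust standard errors are used if residual variances prove heterogeneous. Two sensitivity ANCOVAs use baseline only as a covariate; the weighted completer version is optional and the other uses LOCF.
- **Size (Sample size calculation).** "With a 5% significance level and 90% power, we determined that 48 subjects per group will be required for the trial", for d = 0.68 and an SD of 3.5 on the depression subscale. Recruitment is 140, to allow for up to 30% attrition.

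**The concern.** A single slope for baseline HADS has to serve two purposes. At the baseline visit the score predicts itself with slope 1; at 12 and 36 weeks it predicts a later score with slope ρ. One slope cannot fit both, and the compromise is absorbed by the random-intercept covariance, which maximum likelihood then uses to account for people who leave.

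Three things are at stake in the test that declares efficacy: the precision that baseline adjustment should bring, the type I error once there is dropout, and the assurance that likelihood estimation deals with MAR dropout. That assurance requires a correctly specified model.

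**Working it through.** **Inputs.** From the protocol article: 1:1 allocation, 140 recruited (70 per arm), 48 per arm evaluable, d = 0.68, two-sided 5% assumed (sidedness is not stated), 30% attrition. Not in the documents and therefore assumed: ρ of 0.3, 0.5 and 0.7, equal variances and correlations across visits, dropout after baseline, no site or therapist effects. Results are in SD units.

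**1. The plan's own figure.** n = 2(1.96 + 1.2816)²/0.68² = 45.4, so 46 per arm (47 with the t distribution), close to the stated 48. Then 96/0.70 = 137.1, so 138, against 140 stated. The sample size is reproduced.

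**2. Complete data.** The interaction is a within-person contrast, and a time-constant covariate cancels from it. For one visit:

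- change-score variance is proportional to 2(1−ρ);
- baseline-adjusted variance is proportional to 1−ρ²;
- their ratio is 2/(1+ρ) = 1.54, 1.33 and 1.18 at ρ = 0.3, 0.5 and 0.7.

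Simulation at 70 per arm agrees. The empirical SD of the estimate is 0.193, 0.172 and 0.131 with the covariate, and the same without it. With baseline used once it is 0.158, 0.152 and 0.122. Type I error as written is about nominal (0.05 to 0.07).

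Single-visit power at 48 per arm and d = 0.68 is 0.804, 0.915 and 0.990 for the change score, against 0.937, 0.970 and 0.997 with adjustment.

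**3. The covariance, at ρ = 0.5.** The pooled slope is (1 + 0.5 + 0.5)/3 = 0.667. The residuals then have:

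- variance at baseline (1 − 0.667)² = 0.111;
- variance at follow-up (0.5 − 0.667)² + 0.75 = 0.778;
- baseline–follow-up covariance 0.333 × (−0.167) = −0.056;
- covariance between the follow-ups 0.028 + 0.25 = 0.278.

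A random intercept averages these. The mean covariance is (−0.056 − 0.056 + 0.278)/3 = 0.056 and the mean variance (0.111 + 0.778 + 0.778)/3 = 0.556, so the fitted correlation is 0.10, as in the simulations. The correct correlation of the two follow-ups given baseline is (0.5 − 0.25)/(1 − 0.25) = 0.33.

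With complete data the errors offset: the modelled variance of change, 2 × 0.556 × (1 − 0.10) = 1.0, equals the true 2(1 − 0.5) = 1.0. With dropout they do not. Follow-up means rest on fewer people, yet are given residual variance 0.556 instead of 0.778. For someone seen only at baseline, the follow-up is predicted with slope 0.667 + 0.10 × 0.333 = 0.70 instead of 0.50.

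**4. Type I error with dropout** (70 per arm, no true effect, 2,500 replicates; Monte Carlo SE √(0.05 × 0.95/2500) = 0.004):

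| ρ | Dropout | Model SE / empirical SD, as written | Error, as written | Error, baseline used once |
|---|---|---|---|---|
| 0.3 | 30%, random | 0.207 / 0.226 | 0.094 | 0.052–0.054 |
| 0.3 | 30%, same baseline dependence | 0.205 / 0.229 | 0.089 | 0.059–0.060 |
| 0.5 | 30%, random | 0.176 / 0.199 | 0.085 | 0.059–0.064 |
| 0.5 | 30%, same baseline dependence | 0.175 / 0.195 | 0.092 | 0.055–0.061 |
| 0.7 | 30%, random | 0.137 / 0.153 | 0.087 | 0.051 |
| 0.7 | 30%, same baseline dependence | 0.137 / 0.154 | 0.088 | 0.051–0.058 |
| 0.5 | 40% control, 20% CaCBT, same dependence | 0.177 / 0.192 | 0.092 | 0.051–0.052 |

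**5. Bias (true effect zero).**

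- Same rate and same baseline dependence in both arms: at most 0.004 SD.
- 40% against 20% dropout, unrelated to baseline: about 0.
- 40% against 20%, same baseline dependence: 0.054, 0.036 and 0.024 SD at ρ = 0.3, 0.5 and 0.7.
- Opposite dependence by arm (logit of dropout −0.95 ± 0.8 per SD of baseline, ρ = 0.5): 0.11 SD, with type I error 12–14% across ρ.

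Where high-baseline controls leave more often, the bias favours CaCBT. Dropping the covariate removes nearly all of it, so the double use is the cause.

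**The case against.** The strongest defence has four parts.

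- **The complete-data test is valid.** It is a change-score test with about nominal error, and the trial was sized on between-group change. This stands: the loss there is of efficiency only.
- **The plan has a repair for the standard errors.** The double use produces very unequal residual variances (0.111 against 0.778 above), which is what the residual check looks for. With robust errors, simulated type I error fell from 9.1% to 5.5% (same dropout in both arms), 9.2% to 6.1% (random) and 9.9% to 6.5% (unequal rates); a repeat gave 6–7%. This largely stands, but the rule is conditional and does not remove bias. In the opposite-direction case the error fell only from 13.9% to 9.9%.
- **Baseline is used once in the sensitivity ANCOVAs.** True, but they do not decide efficacy.
- **The covariance structure may be set in the full analysis plan.** It may, but freeing it would not rescue this mean model: with slope 1 the baseline residual vanishes and the likelihood has no proper maximum.

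A reader might infer that the test is biased whenever dropout depends on baseline. It is not; the slope error cancels when rate and dependence are the same in both arms. The Background and Discussion do expect fewer dropouts with CaCBT, but they speak of leaving therapy, not of missing assessments, and nothing suggests opposite dependence by arm. That case is a stress test.

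**Conclusion.** The double use of baseline is explicit and sits in the deciding analysis. It should be fixed, though it does not invalidate the design. The covariate buys no precision in the deciding test, at a cost of about one third more variance at ρ = 0.5. At the attrition planned for, model-based type I error is about 9–10%, or 6–7% if robust errors are triggered. Bias is about 0.04 SD with roughly 40% against 20% baseline-dependent dropout, 0.11 SD in the stress case, and essentially nil when dropout is alike in both arms.

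The MAR assurance therefore does not hold for this model. Adding dropout predictors as main-effect controls does not restore it, since baseline HADS is already in the model in that form and the bias remains.

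Two further inferences are not supported. The 48 per group is not undermined: it was sized without credit for adjustment, and the change-score contrast falls below 90% power only if ρ is under about 0.5. Nor can these sizes be turned into points on the analysed outcome: 3.5 is the depression-subscale SD, while this model analyses total HADS, whose SD is not given. All sizes depend on the assumed correlation and dropout models.

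**What to change.** Use baseline HADS once, in either of two ways.

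1. Keep baseline, 12 and 36 weeks as responses, constrain the arms to a common baseline mean, and remove the baseline covariate. Efficacy is the joint test of the group differences at 12 and 36 weeks. This keeps every randomised participant with a baseline score in the model, in line with the intention-to-treat statement.
2. Model 12 and 36 weeks only, with baseline HADS and baseline-by-time as covariates. Efficacy is then the joint test of the group effects at the two visits. The wording must change accordingly, because group-by-time alone would then test only whether the effect differs between 12 and 36 weeks. Participants with no post-baseline score do not contribute.

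In both, keep gender and the planned site and therapist terms; the therapist term matters because, under Training and fidelity, each therapist delivers only one of the treatments. In the simulations both versions had bias of about 0 (at most 0.006 SD) under baseline-dependent dropout and type I error of 0.05 to 0.08.

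The cost is a few sentences of analysis text. No new data, visits or participants are needed.

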##### Measurements

Assessments will be carried out at baseline after therapy has been completed (12 weeks from baseline) and at follow-up (36 weeks from baseline) by raters blinded to group allocation. The primary outcome, the effectiveness of the psychotherapy addressing levels of depression and anxiety, will be measured using the HADS Depression subscale [37]. HADS is a 14-item, self-assessment scale designed to measure anxiety and depression. The maximum score is 21 for depression and 21 for anxiety. A score of 8–10 suggests the presence of the borderline cases, while a score of 11–21 indicates probable cases. Secondary outcomes, including somatic symptoms, disability, feasibility, acceptability and satisfaction, will also be measured. The Bradford Somatic Inventory (BSI) enquires about a wide range of somatic symptoms during the previous month and has 45 items. Scores above 21 indicate depression [38]. Disability will be measured using the World Health Organization’s Disability Assessment Schedule 2.0 (WHODAS) [39]. This scale assesses disability due to physical and psychological problems and has been used extensively in various research settings. Feasibility will be measured through engagement, recruitment and retention of participants. Acceptability will be measured through feedback from participants and therapists. Participants will also be asked to report their satisfaction by responding to the Verona Service Satisfaction Scale [40]. The Working Alliance Inventory (WAI) [41] will be used to measure therapeutic alliance.

A questionnaire adapted from Beecham and Knapp’s [42] costing psychiatric interventions measurement protocol will be used to ascertain health and social service utilization relevant from the perspective of the health system and participant perspectives. The questionnaire filled out by participants at baseline will inquire on service utilization in the past 6 months. The questionnaires at 3 and 9 months post-treatment will inquire about service utilization in the past 3 and 6 months. Information on outpatient and emergency department visits, hospitalizations and medications, visits to community organizations and receipt of social services will be collected. Participant out-of-pocket costs for seeking health and social services will also be considered and include drug co-payments, direct payments to professionals not covered by public insurance plan, cost related to transportation and time spent by patients while consulting.

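### The success rule rests on the whole group-by-time interaction and fixes neither visit nor direction, while the sample size was set for one end-of-trial difference

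*Protocol article*

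**What the plan says.** The Protocol article's Statistical analyses section describes a mixed model in which assessment occasion (baseline, week 12, week 36), arm and their interaction are fixed factors. The interaction is the success criterion: its significance "tests for difference in HADS score at 3 or 6 months and will be used to declare the intervention effective". Later the section adds: "A significance level of 0.05 will be used to declare the CaCBT performs better than standard CBT".

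The Sample size calculation section has a different target. "The sample size was calculated using a comparison between group change in the HADS Depression subscale scores", and the effect to be detected is a "difference in HADS score at the end of the trial of around 2.4 points", with an SD of 3.5 and a Cohen's d of 0.68. "With a 5% significance level and 90% power, we determined that 48 subjects per group will be required for the trial".

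The Measurements section puts the post-baseline assessments at "12 weeks from baseline) and at follow-up (36 weeks from baseline". The economic evaluation labels its observation periods 3 and 9 months.

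**The concern.** A joint interaction test asks whether the arms differ in their pattern of change over the three occasions. It is significant for a benefit at both visits, for a benefit at one visit only, and for a benefit at one visit with harm at the other. The plan attaches the conclusion that CaCBT performs better to that test without adding a visit or a sign. The sample size section thinks of success as a single difference at a single time, but leaves that time open.

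At stake is the trial's main claim. A significant interaction could be reported as effectiveness when nothing remains at week 36, or when the two visits point in opposite directions. Nothing in the stated rule settles which visit carries the conclusion.

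**Working it through.** **1. The planned sample size.** Inputs from the Sample size calculation section: d = 0.68, alpha 5%, power 90%. Sidedness is not stated; two-sided is assumed because it comes closest.

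n per arm = 2(1.960 + 1.282)² / 0.68² = 2 × 10.507 / 0.4624 = 45.4, so 46. The t-based value is 46.4, so 47. One-sided testing would give 37 to 38. The stated 48 therefore fits one two-sided comparison of two means, with power of about 0.91 at 48 per arm. It is a single-contrast calculation.

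**2. Degrees of freedom of the rule.** Occasion has three levels and arm has two: (3 − 1)(2 − 1) = 2. The article does not print this number. It follows from entering time as a factor.

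**3. How often the rule is met.** Let a and b be the CaCBT advantage in change from baseline at weeks 12 and 36. With n per arm, SD σ and equal correlation r between occasions, the noncentrality is

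λ = (n/2) × (2/3)(a² − ab + b²) / [σ²(1 − r)].

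With n = 48 and σ = 3.5, λ = 16(a² − ab + b²) / [12.25(1 − r)]. The rejection probability is that of a noncentral F with 2 and 2(2 × 48 − 2) = 188 degrees of freedom. The article gives no r, so r = 0.5 is assumed, with a range of 0.3 to 0.7.

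- a = 2.4, b = 2.4: a² − ab + b² = 5.76, λ = 16 × 5.76 / 6.125 = 15.05
- a = 2.4, b = 0: also 5.76, so λ = 15.05 again
- a = 1.2, b = −1.2: 3 × 1.44 = 4.32, λ = 16 × 4.32 / 6.125 = 11.28

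| Advantage at week 12, week 36 | Rule met, r = 0.5 (0.3 to 0.7) | Week-12 contrast alone, r = 0.5 | Week-36 contrast alone, r = 0.5 |
|---|---|---|---|
| 2.4, 2.4 | 0.94 (0.84 to 0.996) | 0.92 | 0.92 |
| 2.4, 0 | 0.94 (0.84 to 0.996) | 0.92 | 0.05 |
| 1.2, −1.2 | 0.86 (0.71 to 0.98) | 0.39 | 0.39 |
| 0, 0 | 0.05 | 0.05 | 0.05 |

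The joint test cannot tell the first row from the second: the noncentrality is identical. In the third row the two visits contradict each other, and the rule is still usually met.

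**4. Visit labels.** At 4.345 weeks per month, week 12 is 2.8 months and week 36 is 8.3 months from baseline. Week 36 is 24 weeks, or 5.5 months, after the week-12 visit. So 6 months can describe week 36 only if counted from the end of therapy, whereas 3 months for week 12 is counted from baseline. The economic evaluation calls the same two occasions 3 and 9 months. The labels do not share one clock.

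**The case against.** A joint test over two follow-up visits is a legitimate way to control multiplicity, and several stronger criticisms that a reader might infer fail.

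- *Inflated type I error.* No. The joint test rejects 5% of the time when the arms do not differ.
- *No effect estimate.* No. The fitted model gives a group difference in change at each follow-up visit. Only the decision statistic is joint.
- *Wrong-direction rejection as a special defect.* Any two-sided test rejects equally often for an effect of the same size in the other direction, and the plan words its conclusion as CaCBT being better. What remains is narrower: one contrast has a sign to read, while a joint test over two visits has none when the visits disagree.
- *An underpowered trial.* Not shown. For a constant 2.4-point benefit the joint test has power 0.94 at r = 0.5, against the planned 90%, and falls short only at low assumed correlations (0.84 at r = 0.3). Depending on the effect pattern it can have more or less power than a single contrast.
- *Analysis of a visit that is not scheduled.* No. The model description lists weeks 12 and 36, as Measurements does. The 6-month wording is a mislabel of week 36.

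It is also fair that the 2 degrees of freedom are inferred, and that an SAP not shown may add visit-specific contrasts. But the success criterion is not left to another document. The article states it, and states it without visit or direction.

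**Conclusion.** The point holds as a mismatch between the success rule and both the powered quantity and the conclusion drawn. The sample size supports one two-sided contrast at one visit. The rule is a joint test that can be met about 94% of the time (84 to 99.6%) with no difference at week 36, and about 86% of the time (71 to 98%) with effects of opposite sign. A significant interaction alone is therefore not evidence that CaCBT performs better. It also remains unclear whether the powered end-of-trial difference belongs to week 12 or week 36.

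The percentages are illustrative. They assume 48 analysed per arm, complete data, equal correlation between occasions, and no covariates or site or therapist effects. They use the SD and difference given for the HADS Depression subscale, although the Statistical analyses section makes total HADS primary. The structural point does not depend on these assumptions.

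**What to change.** Name one primary visit, 12 or 36 weeks from baseline, and use it consistently in Sample size calculation and Statistical analyses. This includes the sensitivity ANCOVA, which also refers to the end of the trial. Keep the mixed model. Declare effectiveness from the model-based CaCBT minus standard CBT difference at that visit, with its estimate, 95% confidence interval and a two-sided 0.05 test, and only if the difference favours CaCBT. Make the other visit secondary; the interaction test can be reported as supporting information. Replace the 3-or-6-month wording with 12 or 36 weeks from baseline.

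The cost is a change of wording, to be made before unblinding. The stated 48 per group already fits a single contrast, so this change needs no new sample size. The one real loss is that an effect confined to the visit not chosen no longer counts as primary success.
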